### Study treatments

Children in the study will receive either a child-focused therapy approach or the task/context-focused approach for 6 months. All children will return to their regular therapy schedule and approach between 6 months and the 9 month follow-up assessment. Table 1 outlines the primary components of each therapy treatment. Children will receive 18 – 24 sessions of therapy over the 6-month study period. Parent education and consultation about general disability information regarding their child will be provided to both treatment groups.

**Table 1 T1:** Comparison of Process and Components of Child-Focused and Context-Focused Approaches

**Factor**	***Context-Focused Approach***	***Child-Focused Approach***
Location	Home or community setting	Outpatient or community setting

Therapist	Physical or occupational therapist (prime therapist model) Only one therapist providing intervention (other therapists available for consultation and development of treatment plan)	Regular physical therapist and/or occupational therapist May have more than one therapist

Goal Identification	Parent defines goals based on identification of transitions using the COPM	Therapist sets goals after discussion with parent, teachers, etc.

Assessment Process	Observe and videotape child performing identified tasks and use the task/context-focused framework for performance analysis to identify barriers and supports to performance. *"Top-down" approach starting with identification of functional goals and then identifying specific constraints that are barriers to achievement of functional goal*	Assess child's current level of functioning in motor, behavioral, functional areas of performance. *"Bottom-up" approach starting with identification of impairments and then identifying functional limitations*

Primary Treatment Strategy	*First target of intervention is to change constraints identified within the task and/or environment* *Work always at activity and/or participation level in the ICF model*. Use success at task as guide to intervention Different movement strategies are expected in different environments	*First target of intervention is a focus on remediation using neurodevelopmental and other regular therapy techniques at the level of body function and structure* *Work from body function and structure in ICF model thus leading to changes in functional activity* Use typical patterns of movement and hierarchical skills as guide to intervention. The movement strategy chosen is expected to generalize across different environments

Frequency	Intermittent and intense, focused on goals identified (typically 3–4 sessions followed by a break before therapy focuses on another task). 18–24 sessions over 6 months.	Regularly scheduled appointments (typically 3–4 times/month). 18 – 24 sessions over 6 months.

### Child-Focused Approach

In the child-focused approach group, the focus of intervention will be on remediation of the child's abilities through changing the components of body function and structure. Therapists trained for this intervention will receive information regarding current intervention topics. For example, for gross motor intervention, therapists will learn how to establish and modify progressive resisted strengthening programs [60], and training programs to improve gross motor performance [61], gait [62], and function [63] using muscle strengthening techniques. Current principles of neurodevelopmental therapy will also be reviewed [9]. Using neurodevelopmental principles, the child is encouraged to develop more normal movement patterns that will assist him/her in achieving the desired goal. Precise therapeutic handling techniques will be used to improve the child's abilities at the component of body function. Goals will be set with the assumption that changes at the level of body function and structure will affect the child's abilities in activity and participation. Environmental adaptations are usually considered only when remediation of the child's abilities is not successful. Therapists in this arm of treatment will receive up to date information about child-focused intervention approaches appearing in the literature, encouraging them to assume a strong evidence based approach to practice.

### Task/Context-Focused Approach

The task/context-focused approach will follow the principles emerging from dynamic systems theory as described above in the literature review. Motor-based tasks, which a child is beginning to do, trying to do differently or showing an interest in doing but having difficulty accomplishing, will be identified by parents using the Canadian Occupational Performance Measure (COPM) assessment [64]. A videotape of each child performing the identified task will be used as the basis for analysis by the therapist and parents. For each task, the next step in the task/context-focused approach is to identify factors in the task, environment and/or child that are hindering the child's performance of the task. Working with the parents, the therapist will identify these constraints through an analysis of observed task performance. Examples of barriers and facilitators will be discussed in the training sessions but an exhaustive list is not provided. Treatment will focus on changing the identified constraints. Therapists will be instructed to change environment and task constraints first to achieve the functional goal. If a specific changeable constraint is identified within the child, intervention may include changing this constraint through time-limited intervention, but only at the level of activity and/or participation.

Intervention will emphasize practice of tasks in natural environments (e.g. home, preschool). It will not focus on the achievement of motor skills within a hierarchical framework or on the achievement of improved quality of movement. Treatment will assist the child in accomplishing the identified functional task with a minimal amount of treatment. Children will be allowed and indeed encouraged to use any compensatory strategies to achieve functional tasks. Therefore spontaneously chosen movement patterns such as W-sitting, scooting, and pulling to standing using arms will be encouraged if they are effective, least intrusive and acceptable to the child. For the task/context-focused approach, we will employ a prime therapist model – one therapist, either an occupational therapist or a physical therapist, will be assigned to each child and will conduct the intervention for that child (with the other therapist providing consultation).

### Delivery of treatment protocols and therapist training

Therapists in both groups will receive one and a half days of study training – the first half-day will focus on the study protocol and will be done together, with therapists in both arms; the second day will be completed separately for each group and will center on implementing the specific components of the task/context-focused approach or child-focused therapy. Expert consultation will be available for therapists in each treatment group. Therapists will have opportunities to discuss case scenarios and view videos of children. For each experience (scenarios, videos), therapists will practice assessing and intervening using the child-focused approach or the task/context-focused approach. The study has clearly defined the key components of each treatment group. We will monitor intervention protocols on an ongoing basis throughout the trial to ensure procedural reliability; as well, the therapists will have access to a consultant, study investigators, and study coordinator for support, problem solving, and resources. Therapists in both treatment groups will complete a short log after each session to document the therapy given. During the study, one therapy session per therapist in each arm will be randomly selected for recording by videotape. These tapes will be evaluated for procedural reliability by trained raters who are occupational therapists or physical therapists. A web-based forum will be developed to encourage regular communication between therapists, the research team and study consultants.

Attendance at therapy appointments will be monitored; those missing a session will be phoned immediately so that another appointment can be scheduled. To measure co-intervention, questionnaires completed by parents and therapists will be used to detail the child's participation in other activities or therapies. As well, we will record any significant illnesses of the children during the 6 month intervention period. If the number of co-interventions or illnesses is not comparable across groups, these data will be included in the analysis as a covariate.

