### Recruitment procedure

Each center in the study has a site coordinator who contacts all therapists to inform them about the study and to obtain their consent to participate. Once therapists have consented to participate in the study they will be block randomized by the coordinating site (by OT or PT discipline) into either treatment arm. On behalf of the research team, each center in the study will mail information that will describe the study to eligible families. Families will be asked to read over the information and indicate their interest in the study on a form to be returned to the research center in a stamped self-addressed envelope. At the baseline visit, study assessors will review the information sheet with the families and witness and co-sign the consent form. Assessors will leave a signed (carbon) copy of the consent form with the family.

Children from consenting families will follow their therapist into the treatment arm that the therapist was randomly assigned to. Due to the nature of the therapy, it will not be possible to keep therapists or parents unaware of the child's treatment group. Therefore, trained, reliable evaluators who are blinded to group assignment will measure all outcomes. Evaluations will be completed at baseline, after 6 months, and at a 3-month follow-up.

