We anticipate that the sample sizes will be approximately balanced between the intervention groups, but if unequal sample sizes occur for some reason, generalized least squares techniques will be used for the statistical analysis. The primary focus will be on the group × time interaction, for which the cluster × time interaction will be used as an error term for testing significance. The statistical significance level will be set at 0.05 for the primary outcome (PEDI assessment). Results will be presented in terms of the estimated mean difference in change between the treatment groups, together with 95% confidence intervals. For secondary outcomes, we will again report means and confidence intervals, but we will be more cautious in our interpretation of these results, recognizing that a large number of statistical comparisons will be made, and also that our power for secondary outcomes may not be as great as for PEDI. Prognostic variables such as age, center and co-intervention, if shown to be important predictors of outcome, will be included in the analysis as covariates. Statistically significant interactions would imply that the treatment effects differ between age and/or severity subgroups. If such interactions are significant, individual contrasts will be examined to determine if there are age/severity subgroups in which treatment differences are statistically and clinically important. An intention to treat analysis will be employed – those who do not adhere to treatment (miss >20% of sessions) will be included in the analysis in their original group. Children who drop out of the study will be included in the analysis in their original group if outcome data can be collected.

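### Co-interventions and illnesses that arise after randomisation can enter the analysis as covariates, which biases the treatment contrast wherever the assigned arm has changed them

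*Protocol article*

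**What the plan says.** Two sections of the protocol article bring variables that arise after randomisation into the model.

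- Delivery of treatment protocols and therapist training: "If the number of co-interventions or illnesses is not comparable across groups, these data will be included in the analysis as a covariate". The data sources are given just before: "To measure co-intervention, questionnaires completed by parents and therapists will be used to detail the child's participation in other activities or therapies", and "we will record any significant illnesses of the children during the 6 month intervention period".
- Analyses: "Prognostic variables such as age, center and co-intervention, if shown to be important predictors of outcome, will be included in the analysis as covariates". This stands in the same paragraph as "An intention to treat analysis will be employed".

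Three other statements bear on whether treatment could change these variables.

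- Recruitment procedure: therapists are randomised, children follow their therapist, and "it will not be possible to keep therapists or parents unaware" of the child's group.
- Study treatments, Table 1: the context-focused arm has "Only one therapist providing intervention", while a child in the child-focused arm "May have more than one therapist".
- Methods/Design: a worrying loss of joint range can lead to a physician referral, and any stretching that follows is recorded.

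Neither covariate rule is labelled as secondary or as a sensitivity analysis.

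**The concern.** Randomisation makes the arms comparable on what existed beforehand. It gives no such guarantee for what happens afterwards. If one arm leads families to seek more, or less, therapy elsewhere, that difference is part of what the assignment did.

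Adjusting for it does two things. It takes out any part of the effect that runs through the extra therapy. It also compares children with equal co-intervention who reached that level for different reasons in each arm. Anything unmeasured that drives both co-intervention and outcome, such as family motivation, then leaks into the group contrast.

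The Delivery rule is triggered by a between-group difference, which is the situation in which an effect of treatment on the covariate is most plausible. What is at stake is the primary PEDI contrast: the adjusted figure would be reported as the treatment effect while answering a different question from the intention-to-treat one.

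**Working it through.** **1. The plan's own figure.** Inputs from Sample size: difference 3 points, SD of change 7, two-sided alpha 0.05, power 80%, cluster size 3, ICC 0.1.

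- n per group before clustering = 2 × [7 × (1.960 + 0.842) / 3]² = 85.5, rounded up to 86.
- Design effect = 1 + (3 − 1) × 0.1 = 1.2.
- 86 × 1.2 = 103.2, rounded up to 104. This matches the plan. Power at 105 per group is 80.9%.

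No covariate enters this calculation, so it does not depend on either rule.

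**2. Formula for the bias.** Take a linear model for the PEDI change score. Let a be the shift in the covariate caused by treatment, and s the within-arm slope of PEDI change on the covariate. Then

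adjusted contrast = total effect − a × s.

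There is no bias on average if a = 0 or s = 0. The Delivery trigger (groups differ) selects on the observed counterpart of a. The Analyses trigger (predicts outcome) selects on s.

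**3. Illustrations.** The document gives no value for a or s, so every value below is assumed. The true total effect is 3. The covariate's within-arm variance is 0.98 in the first two rows and 1 in the others.

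| Situation | a | s | a × s | Adjusted contrast |
|---|---|---|---|---|
| Weak shared cause | 0.2 | ±(2 × 0.3 / 0.98) = ±0.61 | ±0.12 | 2.88 or 3.12 |
| Moderate shared cause | 0.5 | ±(2 × 0.7 / 0.98) = ±1.43 | ±0.71 | 2.29 or 3.71 |
| Covariate carries part of the effect | 0.5 | 2 | 1.00 | 2.00 |
| Strong shared cause, opposite sign | 0.5 | −3 × 0.707 = −2.12 | −1.06 | 4.06 |
| Last two combined | 0.5 | 2 − 2.12 = −0.12 | −0.06 | 3.06 |
| Chance imbalance only | 0 | any | 0 | 3.00 |

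**4. The rule applied to this design.** A simulation used 35 therapists × 3 children per arm, SD 7, ICC 0.1 and 4,000 replicates per scenario. It adjusted only when the covariate differed by arm at p < 0.05; that threshold is an assumption.

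- With a = 0.5 the rule fired in about 95% of trials. Mean estimates under the rule were 2.05 (covariate carries part of the effect), 4.05 (strong shared cause) and 3.05 (both combined).
- With a strong shared cause and a true effect of 0, the mean was 1.05, a spurious benefit.
- With chance imbalance only, the rule fired in 5–6% of trials and the mean was 2.99 to 3.00.
- Without the covariate, the estimate recovered the truth in every scenario (about 3.0, or about 0.0 when the truth was 0).

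**5. Consequence for power.** At 105 per group and SD 7, power is 81% for a 3-point difference and 47% for a 2-point difference. This is indicative only, since adjustment also changes the residual variance.

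**The case against.** Several objections have force.

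- **Imbalance need not come from treatment.** With about 35 therapists per arm, and families approached after therapists are randomised, co-intervention can differ through chance or through who was recruited. This stands. A reader might infer that any between-group difference proves an effect of treatment, or that the rule always biases. The documents do not support that, and chance imbalance gives no average bias.
- **Severity is measured.** GMFCS level is recorded and used to stratify, and the outcome is change from baseline. So severity is a poor example of an unmeasured common cause. Family motivation is a better one, since no planned measure of it is described.
- **Illness has no stated mechanism.** Nothing in the article suggests that either approach alters illness rates. The principle is the same, but the practical risk is smaller.
- **Timing is explicit only for illness.** The co-intervention questionnaires are undated. That they cover the treatment period is an inference from their purpose, though a safe one.
- **The rule is written in advance, and an analysis plan may define comparability.** True, and the missing threshold is not held against the article. Prespecification does not change what the adjusted contrast estimates.
- **This is an efficacy study, so an effect net of other therapy may be wanted.** A single covariate delivers that only if co-intervention and outcome share no unmeasured causes. The article also commits to intention to treat.
- **Some co-interventions are limited by design.** Planned surgery and planned motor-relevant medication changes are exclusions. That narrows the problem; other therapies and unplanned changes remain.
- **Form of the model.** With complete data, a child-level covariate entered only as a main effect in the repeated-measures model would leave the group-by-time contrast unchanged. The bias needs the covariate in the change-score comparison or in interaction with time. The article does not say which is meant, so the exposure remains.

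**Conclusion.** The rules are wrong as written, conditionally on treatment changing the covariate. Unblinded families and different care structures make that plausible for co-intervention and less so for illness. Where it happens, the adjusted contrast is not the intention-to-treat effect that the Analyses section promises.

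Direction and size cannot be determined from the document. Under the assumed inputs the bias runs from about 0.1 to about 1 point in either direction, that is, roughly 4% (0.12 / 3) to 35% (1.06 / 3) of the 3-point target, and opposing mechanisms can nearly cancel. A reader might fix on one value, such as 0.71 points or 24% of the target. That is correct arithmetic on one invented set of inputs and should not be cited as the expected bias.

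A reader might also take the Analyses sentence as the same rule stated twice. It is not: its trigger is prediction of outcome rather than imbalance. The article therefore has two different conditions for admitting one covariate, and a trial could meet one and not the other.

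**What to change.** 1. Delete the rule in Delivery of treatment protocols and therapist training that adds co-interventions or illnesses as covariates.
2. Remove co-intervention from the list of prognostic covariates in Analyses. With step 1, this also removes the two conflicting triggers.
3. State that the primary model adjusts only for variables fixed before randomisation.
4. Report co-interventions and illnesses by arm. If an adjusted estimate is wanted, present it as one labelled sensitivity analysis that does not determine the conclusion.

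The cost is two sentences of wording. Data collection is unchanged, no more children are needed, and the figure of 104 per group stands. Where imbalance is due to chance alone, leaving the covariate out introduces no bias.

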### Measure and data collection procedures

The primary outcome in this study is performance of functional tasks (mobility and self-care) as measured by the Pediatric Evaluation of Disability Inventory (PEDI) [65]. Secondary outcomes include range of motion, gross motor function, participation in everyday activities, health status, parent empowerment, and parents' perceptions of care. Independent evaluators who are unaware of the child's treatment assignment will assess the children and parents/caregivers in their home. Outcome measures in the trial include:

### Body functions and structures (Impairment)

#### 1. Range of motion measure

The independent, trained assessors will take goniometry measurements of hip abduction, popliteal angle, and ankle dorsiflexion ranges of motion of children in both treatment groups. To reduce measurement error, two consecutive measurements will be done of each range of motion and the average calculated.

#### 2. Gross Motor Function Classification System (GMFCS)

The Gross Motor Function Classification System (GMFCS) [66] will be used to classify the gross motor function of children and stratify children based on severity (less severe, levels I and II; more severe, levels III-V). The GMFCS has evidence of very good reliability and validity.

### Activities

#### 1. Pediatric Evaluation of Disability Inventory (PEDI)

The Pediatric Evaluation of Disability Inventory (PEDI) [65] will be used to measure mobility and self-care. The PEDI can be completed by structured interview. Part I: Functional Skills and Part II: Caregiver Assistance will be administered for the Mobility and Self-care Domains. Internal consistency measured by Cronbach's alpha is .99 for the Self-Care domain and .97 for the Mobility domain. Inter-rater reliability (ICC) between interviewers is 1.00 for both domains among rehabilitation therapists; and .88 and .98 when completed by different family members. Evidence of concurrent validity is provided by the high correlations between the Self-Care domain and Wee-FIM Self-Care scores (r = .92) and Mobility domain and Wee-FIM Mobility scores (r = .97). Responsiveness of the PEDI for children with CP was demonstrated over a 4–6 month period for the Self-care and Mobility Domains when assessed by a therapist and in the Self-care Domain when assessed by a parent [67].

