### Sample size

Sample size was calculated for the primary study outcome, using the following: where n = number of subjects per group, **α **= significance level (2-sided testing), **1 - β **= power, **σ **= SD of change within individuals, ICC = intraclass correlation, m = average cluster size, **Δ **= minimum absolute change to be detected, number of clusters (therapists) = n/m. The within-child standard deviation for change on the PEDI scale was set at 7. This value is based on data reported in the PEDI manual, and data from Ketelaar et al. [33]. Specifically, the value 7 is the working average of the within-child standard deviation observed by Ketelaar et al. [33] for self-care functional skills and mobility. We took the average cluster (number of children per therapist) size to be 3, the ICC to be 0.1, and therefore assumed a variance inflation factor (design effect) associated with therapists to be 1.2. The variance inflation factor allows for the possibility that some therapists may be more effective in inducing a change on the PEDI scale compared to other therapists, and takes into account the clustered nature of the sample of participating children. Based on data from our task/context-focused pilot study, we projected an estimated difference in the change scores between the treatment groups of 3 points on the PEDI, and used a two -sided α-value of 0.05, with power of 80%. Our sample size estimates are based on the PEDI because it demonstrates the greatest score variability, and because it is the primary measure of interest in the study. The specifications above lead to a required sample size of 104 children per group, which we rounded to 105 per group so that 35 therapists would be required per group. With additional children to account for dropouts, our target sample size is set at 220.

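### The PEDI primary outcome covers at least two scores, but the plan sets one unshared 0.05 level and sizes the trial for a single score

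*Protocol article*

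**What the plan says.** Four places in the protocol article bear on this.

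- **Measure and data collection procedures** defines the outcome by two domains: "The primary outcome in this study is performance of functional tasks (mobility and self-care", measured by the PEDI.
- **Activities, item 1 (PEDI)** says which parts are collected: "Part I: Functional Skills and Part II: Caregiver Assistance will be administered for the Mobility and Self-care Domains". Two parts in two domains make four scores. Reliability and validity are reported separately for self-care and mobility.
- **Analyses** sets the level for the instrument, not for a named score: "The statistical significance level will be set at 0.05 for the primary outcome (PEDI assessment". The primary focus for testing is the group × time interaction. Caution about the number of comparisons is expressed only for secondary outcomes.
- **Sample size** works with one score: "we projected an estimated difference in the change scores between the treatment groups of 3 points on the PEDI", a two-sided 0.05 and 80% power. It adds "The within-child standard deviation for change on the PEDI scale was set at 7", and describes that value as a working average of the SDs seen in an earlier study "for self-care functional skills and mobility".

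Nowhere does the article name one PEDI score as primary, combine the scores, order them, require all of them, or divide the 0.05 among them.

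**The concern.** Three things the protocol fixes do not fit together: a primary outcome with at least two scores, one significance level, and a sample size for one score. The blended SD shows that more than one score was in view when the trial was sized, yet the calculation has one difference, one SD and one test.

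What the trial may claim depends on the missing rule. If a significant result on any score supports the primary claim, the overall error rate exceeds the stated 5%. If every score must be significant, the error rate is controlled but power falls below the stated 80%. The stated alpha and power are both correct only if a single score or composite is tested, and none is identified. Parents and therapists know the treatment arm, and the PEDI can be completed by interview. That is a further reason to settle the claim-bearing score before data are seen.

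**Working it through.** **Inputs from the Sample size section:** difference 3, SD 7, two-sided alpha 0.05, power 80%, average cluster size 3, ICC 0.1, required n 104 per group rounded to 105.

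**Assumption:** the correlation between the test statistics of different PEDI scores is not given. A range of 0 to 0.9 is used, equal for all pairs. Each score is treated as one two-sided normal test of the between-group difference in change, as in the protocol's own calculation.

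**Step 1: reproduce the stated n.**

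n per group = 2 × 7² × (1.960 + 0.842)² / 3² = 85.5, rounded up to 86.

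Design effect = 1 + (3 − 1) × 0.1 = 1.2.

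86 × 1.2 = 103.2, rounded up to 104. The stated figure is reproduced, for one score tested at 0.05.

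**Step 2: power for one score at 105 per arm.**

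Expected z = 3 / √(2 × 49 × 1.2 / 105) = 2.835.

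- At 0.05: P(Z > 1.960 − 2.835) = 81%.
- At 0.025 (two scores, Bonferroni): 72%.
- At 0.0125 (four scores, Bonferroni): 63%.

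To keep 80% power per score under Bonferroni, two scores need 104 × 1.2 = 124.8, so 125 per group. Four need 122 × 1.2 = 146.4, so 147 per group.

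**Step 3: false-positive rate if any score may win, each at 0.05.** With independent scores it is 1 − 0.95^k: 9.75% for k = 2 and 18.5% for k = 4. Correlated cases come from simulation (2 million draws).

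| Correlation | Two scores | Four scores |
|---|---|---|
| 0 | 9.7% | 18.5% |
| 0.3 | 9.5% | 17.4% |
| 0.5 | 9.0% | 15.5% |
| 0.7 | 8.4% | 13.1% |
| 0.8 | 7.8% | 11.4% |
| 0.9 | 7.0% | 9.4% |

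**Step 4: two scores, 105 per arm, both truly differing by 3 points.** With independent scores, power for both at 0.05 is 0.809² = 0.655, and Holm power for at least one is 1 − (1 − 0.7235)² = 0.92. The other values are simulated in the same way.

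| Correlation | Both significant at 0.05 | Holm, per score | Holm, at least one |
|---|---|---|---|
| 0 | 65% | 79% | 92% |
| 0.5 | 70% | 78% | 86% |
| 0.7 | 72% | 77% | 83% |
| 0.9 | 76% | 76% | 78% |

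Under a both-must-win rule with no effect on either score, the false-positive rate is 0.3% at correlation 0 and 3.0% at 0.9. The cost of that rule is power, not error.

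**The case against.** A reader might infer that all four PEDI scores are tested at 0.05, that any one of them suffices, and that the trial's error rate is therefore 13–19%. The documents do not support this as a flat statement.

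- The PEDI item says only that both parts are administered, which describes data collection. The outcome definition names two domains, and the source of the SD does not mention Caregiver Assistance. A two-score reading is at least as well supported.
- No success rule is stated. Any-one-wins is a possibility, not the plan's rule.
- The 13–19% range needs four scores and correlations of at most about 0.7. At 0.9 the four-score rate is 9.4%.

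A reader might also count the 6-month and 9-month changes as separate tests and inflate the rate further. The Analyses section does compare baseline with both times, but it describes this as estimation. It places the primary testing focus on the group × time interaction in a combined model, so the two times should not be counted as additional 0.05 tests.

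The remaining defence is that sharing alpha among subscales is commonly left to a statistical analysis plan, which is not shown. That is fair as far as the method goes: the absence of Holm or an alpha split is not a finding in itself. It does not dispose of the point. The protocol itself states the primary outcome, its significance level and its sample size, and these do not describe the same test. A later plan could name a single score. If it kept several, it could not make 105 per arm deliver 80% power on each at a controlled 5% using Bonferroni or Holm.

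**Conclusion.** The point holds in a conditional form. The primary outcome has at least two component scores, one undivided 0.05 level is attached to it, and the sample size is right for one score only. The size of the problem depends on a rule the protocol does not give:

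- One score or composite: 5% error and the stated power, provided the 3-point difference and SD of 7 apply to it.
- Any score wins: about 7–10% error for two scores, or 9–19% for four.
- Both domains must be significant: error at or below 5%, but power of about 65–76%.

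These figures rest on assumed correlations of 0 to 0.9, a common 3-point difference and SD of 7 for each score, the protocol's design effect, and the single-contrast test used in its sample size. They are not rates for the two-degree-of-freedom interaction test. The 104 per group is not an arithmetic error.

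**What to change.** Name the primary score or scores before analysis, in the Measures and Analyses sections, and make the Sample size section refer to the same ones. Two options are workable.

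1. **One score or one composite.** Alpha stays at 0.05 and 105 per arm stands, provided the 3-point difference and the SD of 7 are justified for that score. The cost is that the remaining PEDI scores become secondary.
2. **Two primary scores.** Take Functional Skills self-care and Functional Skills mobility, test each with the planned group × time analysis, apply Holm at an overall two-sided 0.05, and make the Caregiver Assistance scores secondary. Restate power at 105 per arm: about 76–79% per score and about 78–92% for at least one, if both truly differ by 3 points. The cost is a stated power per score slightly below 80%.

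Option 2 reads the word mobility in the SD source as the Functional Skills mobility score. The protocol should confirm this. Neither option needs more children, unless 80% power per score is to be kept under option 2.
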